##### Economic evaluation analyses

The economic evaluation will be conducted from the societal perspective as the primary analysis, whilst the Australian health system perspective will be used for sensitivity analyses. The time horizon of the economic analysis is 12 months.

For the economic evaluation, missing cost and effect data will be imputed using multivariate imputation by chained equations with predictive mean matching [21]. The imputation model will include variables differing between groups at baseline as well as those predicting the missingness of follow-up cost and effect data. Cost and effect differences will be estimated using seemingly unrelated regression analyses, in which two regression equations are modelled simultaneously and cost and effect differences are adjusted for their possible correlations through correlated error terms. Cost and effect differences will be adjusted using the same covariates as the primary effectiveness analyses, in addition to work status and baseline utility values for QALYs [22]. To handle the right skewed nature of cost data, uncertainty surrounding cost differences will be estimated using bias-corrected and accelerated bootstrapping (5000 replications) [23].

Incremental cost-effectiveness ratios (ICERs) will be calculated by dividing the between-group difference in costs by the between-group difference in effects (i.e. cost per recurrence prevented, and cost per QALY gained). The uncertainty surrounding ICERs will be estimated using bootstrapping as well (5000 replications) and graphically presented on cost-effectiveness planes. Cost-effectiveness acceptability curves will be estimated to show the probability of the intervention being cost-effective for a range of willingness to pay (i.e. maximum amount decision-makers are willing to pay per unit of effect gained). Sensitivity analyses will be performed to assess the robustness of the results based on a complete-case analysis and an analysis from the Australian health system perspective.

##### Physical activity data analyses

To test the effects of the intervention on physical activity, between-group comparisons will be conducted using linear regression at timepoints at which each set of data will be collected (i.e. month 3 for Actigraph data; and at baseline, month 3 and month 12 for the International Physical Activity Questionnaire (IPAQ) data). Transformations will be applied to meet model assumptions, if needed. A template has been provided for how the data will be reported (see Table 2).

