**Methods:**

WalkBack is a prospectively registered, pragmatic, randomised controlled trial. The aim is to investigate the effectiveness and cost-effectiveness of a 6-month progressive and individualised walking and education program (intervention) for the prevention of low back pain recurrences, compared to a no-treatment control group. The primary outcome is days to the first recurrence of an episode of activity-limiting low back pain. Key secondary outcomes include days to any recurrence of low back pain, days to a care-seeking recurrence of low back pain, disability level, health-related quality of life, costs associated with low back pain and adverse events. All participants will be followed for a minimum of 12 months. Analysis will follow the intention-to-treat principle. Cox regression is planned to assess the effects for the outcomes of time to activity-limiting, minimal and care-seeking recurrence. Hazard ratios and median survival times with 95% confidence intervals will be calculated. The effect of the intervention on continuous outcomes will be estimated with repeated-measure linear mixed models. An economic evaluation will be performed from the societal perspective for recurrence prevented (yes/no) and quality-adjusted life years. The proportion of adverse events between groups will be compared using Fisher’s exact test.

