##### Physical activity outcomes

Daily walking will be measured via a hip-worn triaxial accelerometer (Actigraph GTX3), proven accurate and valid for quantifying physical activity [13]. All participants, regardless of treatment group allocation, will be instructed to wear the activity monitor for a 7-day window, 3 months following enrolment to the trial. This outcome will be collected via an objective data source to demonstrate any potential differences in physical activity between the intervention and control groups following 3 months of involvement in the walking intervention.

To source valid physical activity data, we will identify a valid wear day as ≥ 10 h and include participants with at least 4 valid wear days, which is the minimum number of days needed to reliably estimate free-living physical activity [14]. We are specifically interested in the following physical activity parameters:

*Steps per day*. Steps per day will be averaged across the available valid days, for a minimum of 4 days and a maximum wear time of 7 days.*Brisk steps per day*. Brisk walking will be defined as a cadence > 100 steps per minute in accordance with previous literature [15]. Brisk steps per day will be averaged across the available valid days, for a minimum of 4 days and a maximum wear time of 7 days.*Minutes of moderate to vigorous physical activity (MVPA).*Time spent in activity of a defined intensity (MVPA) will be determined by summing minutes in a day where the count met the pre-set criterion based on previous literature and recommendations from the ActiGraph Group [14]. Mean daily time in MVPA will be averaged across the available valid days, for a minimum of 4 days and a maximum wear time of 7 days.

A self-report measure of physical activity will also be collected from all participants (intervention and control), using a modified version of the International Physical Activity Questionnaire – Short Form (IPAQ-SF) [16].

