Perceived risk of recurrence (0 to 10)	xx.x (SD), *n*	xx.x (SD), *n*
Levels of physical activity (IPAQ)		
Walking (min/week)	xx.x (SD), *n*	xx.x (SD), *n*
Moderate (min/week)	xx.x (SD), *n*	xx.x (SD), *n*
Vigorous (min/week)	xx.x (SD), *n*	xx.x (SD), *n*
Time sitting (min in average weekday)	xx.x (SD), *n*	xx.x (SD), *n*
DASS-21 (0 to 21)		
Depression	xx.x (SD), *n*	xx.x (SD), *n*
Anxiety	xx.x (SD), *n*	xx.x (SD), *n*
Stress	xx.x (SD), *n*	xx.x (SD), *n*
Sleep quality		
Very good	xx.x (SD), *n*	xx.x (SD), *n*
Fairly good	xx.x (SD), *n*	xx.x (SD), *n*
Fairly bad	xx.x (SD), *n*	xx.x (SD), *n*
Very bad	xx.x (SD), *n*	xx.x (SD), *n*
Health Status (Euro-QOL)		
EQ-5D-5L Health State Index	xx.x (SD), *n*	xx.x (SD), *n*
EQ-VAS score (0–100)	xx.x (SD), *n*	xx.x (SD), *n*

*BMI* Body mass index, *DASS-21* Depressions Anxiety Stress Scale, *EQ-5D-5L* EuroQol 5-Dimension 5-Level, *IPAQ* International Physical Activity Questionnaire, *VAS* Visual analogue scale, *QOL* Quality Of Life, *kg* kilogram, *m* metre, *SD* Standard Deviation

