#### Secondary analyses

##### Effectiveness outcome analyses

For the outcomes of *any LBP recurrence* or a *care-seeking recurrence of LBP*, an analogous survival analysis to that of the primary outcome detailed above will be conducted.

To test the effects of the intervention on continuous secondary outcomes, between-group comparisons will be conducted using multiple linear mixed-effects regression combining all available post-randomisation measurements (at either months 3, 6, 9 or 12 depending on outcome collection). Transformations will be applied to meet model assumptions, if needed. Linear mixed modelling will be used to take account of the correlation between measurements within an individual for repeated measurements over time. A template has been provided for how the data will be reported (see Table 2).

**Table 2 Tab2:** Secondary outcomes

	**Intervention (*****n***** = xxx)**	**Control (*****n***** = xxx)**	**Mean difference (95% CI), *****p*****-value**
Disability—RMDQ			
Month 3	xx.x (SD), *n*	xx.x (SD), *n*	xx.x (xx.x to xx.x),* p* = 0.xxx
Month 6	xx.x (SD), *n*	xx.x (SD), *n*	xx.x (xx.x to xx.x),* p* = 0.xxx
Month 9	xx.x (SD), *n*	xx.x (SD), *n*	xx.x (xx.x to xx.x),* p* = 0.xxx
Month 12	xx.x (SD), *n*	xx.x (SD), *n*	xx.x (xx.x to xx.x),* p* = 0.xxx
Health-related QoL – EQ-5D-5L			
Month 3	xx.x (SD), *n*	xx.x (SD), *n*	xx.x (xx.x to xx.x),* p* = 0.xxx
Month 6	xx.x (SD), *n*	xx.x (SD), *n*	xx.x (xx.x to xx.x),* p* = 0.xxx
Month 9	xx.x (SD), *n*	xx.x (SD), *n*	xx.x (xx.x to xx.x),* p* = 0.xxx
Month 12	xx.x (SD), *n*	xx.x (SD), *n*	xx.x (xx.x to xx.x),* p* = 0.xxx
Self-reported Physical Activity—IPAQ			
Month 3	xx.x (SD), *n*	xx.x (SD), *n*	xx.x (xx.x to xx.x),* p* = 0.xxx
Month 12	xx.x (SD), *n*	xx.x (SD), *n*	xx.x (xx.x to xx.x),* p* = 0.xxx
ActiGraph measure at 3 months^a^			
Steps per day	xx.x (SD), *n*	xx.x (SD), *n*	xx.x (xx.x to xx.x),* p* = 0.xxx
Brisk Steps per day^b^	xx.x (SD), *n*	xx.x (SD), *n*	xx.x (xx.x to xx.x),* p* = 0.xxx
MVPA minutes per day	xx.x (SD), *n*	xx.x (SD), *n*	xx.x (xx.x to xx.x),* p* = 0.xxx

*EQ-5D-5L* EuroQol 5-Dimension 5-Level, *IPAQ* International Physical Activity Questionnaire, *MVPA* Moderate-vigorous physical activity, *RMDQ* Roland-Morris Disability Questionnaire

^a^Data in above table represents a minimum 4-day, and maximum of 7-day wear period. Only data for participants whose dataset met the minimum wear time requirement of 10 h/day are included

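### Baseline should not be listed as a visit at which the effect on IPAQ activity is tested, and the plan should name one model for the month 3 and month 12 IPAQ comparisons

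*SAP article*

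**What the plan says.** The SAP article speaks to the IPAQ analysis in five places.

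- *Physical activity data analyses* opens: "To test the effects of the intervention on physical activity, between-group comparisons will be conducted using linear regression at timepoints". For the questionnaire the visits are "at baseline, month 3 and month 12 for the International Physical Activity Questionnaire (IPAQ) data". It sends the results to Table 2. It does not say that baseline IPAQ is a covariate or is there only for description.
- *Effectiveness outcome analyses* says of continuous secondary outcomes that "between-group comparisons will be conducted using multiple linear mixed-effects regression combining all available post-randomisation measurements". It presents Table 2, titled Secondary outcomes, as the reporting template.
- The abstract's *Methods* says: "The effect of the intervention on continuous outcomes will be estimated with repeated-measure linear mixed models". No outcome is exempted.
- Table 2 has a block headed "Self-reported Physical Activity—IPAQ" with rows for months 3 and 12, each with a mean difference, confidence interval and p-value. It has no baseline row.
- Table 1 reports baseline IPAQ by arm as mean and SD for walking, moderate activity, vigorous activity and sitting, with no column for a difference or p-value.

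**The concern.** There are two separate problems.

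First, the sentence that sets out the effect tests includes a visit before the intervention begins. With randomised arms, any difference there is due to chance. The sentence also disagrees with the table it cites.

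Second, the text can be read as giving IPAQ two models: a mixed model over the follow-up visits, and separate regressions visit by visit. Both passages point to the same rows of Table 2. The two approaches can use different participants when a visit is missed, and so can give different estimates and p-values for the same row. Increasing physical activity is a stated secondary objective, and the article's conclusion says the plan is meant to limit data-driven reporting. An open choice of model works against that aim. The section also leaves unused, as far as it states, a baseline value that is already collected and could sharpen the follow-up comparisons.

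**Working it through.** The plan gives no numerical figure for the IPAQ analysis, so there is none to reproduce. The design figure of 698 participants concerns the primary outcome and does not enter here. The check is mainly a comparison of passages.

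**Step 1: visits and methods side by side.**

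| Place in SAP article | What it gives for IPAQ | Visits |
|---|---|---|
| Abstract, Methods | Repeated-measures mixed model (all continuous outcomes) | Not listed |
| Effectiveness outcome analyses | Mixed model, if IPAQ counts as a continuous secondary outcome | Post-randomisation only |
| Physical activity data analyses | Linear regression at each visit | Baseline, 3, 12 |
| Table 1 | Description by arm | Baseline |
| Table 2 | Difference, CI, p-value | 3, 12 |

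Only one place has a between-group comparison at baseline. Neither table has a cell for its result.

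**Step 2: does the mixed-model section reach IPAQ?** It describes its model as "combining all available post-randomisation measurements (at either months 3, 6, 9 or 12 depending on outcome collection". The continuous outcomes listed under *Secondary effectiveness outcomes* are the RMDQ and EQ-5D-5L, both collected quarterly across 12 months, so their schedules do not differ. In Table 2 only the physical activity outcomes have another schedule: months 3 and 12 for IPAQ, month 3 for ActiGraph. The qualifier about collection times is easiest to explain if the section was meant to extend to them. This is suggestive, not conclusive.

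**Step 3: whom the choice of model affects.** Inputs: 1% loss per month (*Sample size and randomisation*) and 701 randomised. Assumption: IPAQ is lost at the same rate and no one returns. The plan made that allowance for its sample size calculation, not for IPAQ, so this is an illustration.

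- Still observed at month 3: 0.99^3 = 0.970.
- Still observed at month 12: 0.99^12 = 0.886.
- Observed at month 3 but not at month 12: 0.9703 − 0.8864 = 0.0839, and 0.0839 × 701 ≈ 59 participants.

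A month 12 regression would omit about 11% of those randomised (1 − 0.886 = 0.114). The 59 would still contribute their month 3 value to a mixed model. With complete data at both visits and no covariates, a mixed model with arm, visit and arm-by-visit terms gives the same visit-specific differences as separate regressions. The two diverge only through incomplete participants.

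**Step 4: what baseline adjustment does.** If ρ is the correlation between baseline and follow-up IPAQ, adjusting for baseline multiplies the residual variance of the comparison by about 1 − ρ². The documents do not give ρ, so the gain cannot be sized. It is a gain in precision: the unadjusted randomised comparison is already unbiased.

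**The case against.** The strongest reply is that the document's structure settles both matters. IPAQ is introduced under *Physical activity outcomes*, not under *Secondary effectiveness outcomes*, and *Physical activity data analyses* is the matching analysis section. The specific section then governs, and the abstract is only a condensation. A place in Table 2 does not assign a model either, because the table also holds the single-visit ActiGraph rows, for which a repeated-measures model makes no sense. Baseline may appear only because the parenthesis lists when each set of data is collected.

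Much of this stands. The headings do allow visit-by-visit regression to be read as the intended IPAQ model, and the baseline entry may be a loose list of collection times. But the document states no order of precedence, the abstract makes no exception, and the sentence containing the list is about testing effects. The text still needs correcting.

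Three stronger readings are not supported:

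- A reader might infer that a chance baseline gap will be reported as an effect. Neither Table 1 nor Table 2 provides a place for such a test.
- A reader might attach a false-positive probability by counting the four IPAQ variables in Table 1 as independent tests. The plan never says four variables will be tested, Table 2 has one IPAQ entry per visit, and items from a single questionnaire are unlikely to be independent.
- A reader might infer that a baseline gap biases the month 3 and month 12 comparisons. Under randomisation, lack of adjustment costs precision and does not introduce bias.

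**Conclusion.** The point holds in a limited form. As written, the list of visits for the IPAQ effect test wrongly includes baseline and does not match Table 2. Separately, the abstract, and arguably the effectiveness section through Table 2, prescribes a mixed model where the physical activity section prescribes separate regressions with no stated use of baseline. The baseline error does not follow from the model conflict; each stands alone.

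The severity is low. IPAQ is a self-reported secondary measure, and neither the primary analysis nor the sample size depends on it. What is gained by correcting the text is one prespecified answer per IPAQ row, the use of participants who miss one visit, and some precision from the baseline value. The figure of about 59 rests on borrowing the sample-size loss allowance for IPAQ with no returns after loss. The size of the precision gain cannot be given without the baseline–follow-up correlation.

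**What to change.** 1. In *Physical activity data analyses*, remove baseline from the visits at which arms are compared for an effect. Baseline IPAQ stays in Table 1 as description.
2. State one IPAQ model: a repeated-measures linear mixed model of months 3 and 12 with arm, visit and arm-by-visit terms and baseline IPAQ as a covariate, reporting the difference at each of the two visits. The covariate must be written in, because the effectiveness section does not mention baseline adjustment either.
3. Keep linear regression for the ActiGraph outcomes, which are measured once, at month 3.
4. Align the abstract, *Effectiveness outcome analyses* and *Physical activity data analyses* with Table 2, so that each row has one named model.

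The cost is a change of SAP wording. The baseline and follow-up data are already part of collection, and no visit, sample size or primary analysis changes. The change should be recorded before group allocation is unmasked.

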##### Adverse event analyses

For the measures of adverse events, we will represent the frequency and proportion of participants who experienced an adverse event, and these will be compared between groups using Fisher’s exact test as we expect the incidence of adverse events to be low (see Table 3).

**Table 3 Tab3:** Adverse and serious adverse events

	**Intervention group (*****n***** = xxx)**	**Control group (*****n***** = xxx)**	***p*****-value**
Serious adverse events			
Total	nEVT/nPAT (%)	nEVT/nPAT (%)	*p* = 0.xxx
Adverse event A^a^	nEVT/nPAT (%)	nEVT/nPAT (%)	
Adverse event B^a^	nEVT/nPAT (%)	nEVT/nPAT (%)	
Adverse event C^a^	nEVT/nPAT (%)	nEVT/nPAT (%)	
Etc.^a^	nEVT/nPAT (%)	nEVT/nPAT (%)	
Adverse events			
Total	nEVT/nPAT (%)	nEVT/nPAT (%)	*p* = 0.xxx
Adverse event A^a^	nEVT/nPAT (%)	nEVT/nPAT (%)	
Adverse event B^a^	nEVT/nPAT (%)	nEVT/nPAT (%)	
Adverse event C^a^	nEVT/nPAT (%)	nEVT/nPAT (%)	
Etc.^a^	nEVT/nPAT (%)	nEVT/nPAT (%)	

^a^Example categories which will be revised based on observation of final free-text data responses

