### Study overview

#### Objectives

The primary objective is to determine the effectiveness of a progressive and individualised walking and education program compared to a no-treatment control group, for reducing recurrences of LBP (primary outcome). The trial hypothesis is that the participants randomised to the intervention arm will experience a greater number of days from the time of randomisation to the first self-reported recurrence of an episode of LBP (i.e. superiority). The null hypothesis is that there is no difference in days to the first self-reported recurrence between the two arms of the trial.

Secondary objectives include determining whether the walking and education program:Improves health-related quality of life and disability.Is cost-effective from a societal perspective, including data on healthcare utilisation and productivity loss (work absenteeism) due to LBP.Increases levels of physical activity.Is acceptable and adhered to, based on a series of compliance measures.Results in any greater risk of adverse events when compared to no treatment.

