##### Adverse events outcomes

Adverse event data will be self-reported and collected at quarterly intervals (months 3, 6, 9 and 12). The following definitions will be used:

*Adverse event*, any untoward medical occurrence in a participant that does not necessarily have a causal relationship with this treatment.*Serious adverse event*, any adverse event that resulted in death, was life-threatening, required hospitalisation, or resulted in persistent or significant disability or incapacity. These events do not necessarily have a causal relationship with the treatment.

Adverse events and serious adverse events will be coded according to the International Classification of Diseases (ICD-11) using three-digit codes [17].

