### Statistical analysis

#### Analysis principles

All analyses will be conducted using R software (version 4.2.2 or above) or STATA (version 17.0 or above). Analyses of the primary and secondary outcomes will be conducted by a statistician (member of the trial team), taking no part in participant recruitment or data collection. Analyses will follow intention-to-treat principles, with all participants analysed according to their randomised allocation. A masked sample of the data will first be used to trial and confirm statistical procedures. Next, the fully masked dataset will be used, with data interpretation occurring prior to unblinding of group allocation. There is no intention to conduct interim analyses.

Categorical variables will be summarised by frequencies and percentages. Continuous variables will be reported using standard measures of central tendency and dispersion, either mean and standard deviation (SD) or median and interquartile range, depending on the shape or skewness of the data. A *p*-value < 0.05 will be considered statistically significant. A 95% confidence interval (CI) will be reported to aid the interpretation of precision and the clinical importance of findings.

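### The adverse-event definition does not exclude back pain recurrences, so the tested total can mix prevention benefit with harm, and Table 3 gives no risk difference or confidence interval

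*SAP article*

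**What the plan says.** One secondary objective (SAP article, Objectives) is to learn whether the programme "Results in any greater risk of adverse events when compared to no treatment".

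Under Adverse events outcomes, an adverse event is "any untoward medical occurrence in a participant that does not necessarily have a causal relationship with this treatment". Events are self-reported each quarter. The section adds that "Adverse events and serious adverse events will be coded according to the International Classification of Diseases (ICD-11) using three-digit codes". It neither includes nor excludes a recurrence of low back pain.

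Under Adverse event analyses, "we will represent the frequency and proportion of participants who experienced an adverse event", and the arms are compared by Fisher's "exact test as we expect the incidence of adverse events to be low". Table 3 has one column per arm (events, participants, percentage) and a p-value column. Rows cover all serious adverse events, all adverse events and individual event types; p-values appear on the two totals only. The event types are "Example categories which will be revised based on observation of final free-text data responses".

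Analysis principles states a general rule: "A 95% confidence interval (CI) will be reported to aid the interpretation of precision and the clinical importance of findings". Table 2, for the secondary outcomes, has a column for the difference with its 95% CI. Table 3 has none.

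**The concern.** There are two linked weaknesses.

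First, an episode of back pain is an untoward medical occurrence, so the definition read literally covers the event that the programme is meant to prevent. The sample size section plans for 30% activity-limiting recurrence in controls, and the secondary outcome of any recurrence has a lower threshold still. That does not sit with an expected low incidence. Either recurrences are not meant to count and the rule is unwritten, or they do count and the stated reason for Fisher's test fails. Because the categories are to be settled from the final free text, the choice could fall after the data have been seen.

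Second, the objective asks about added risk, but the only planned between-group result is a p-value. When events are few, a non-significant result is compatible with a real increase, and Table 3 would not show how large an increase remains possible.

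At stake is the trial's statement on safety. A true rise in other events could appear as a smaller difference, as no significant difference, or in the worst case as fewer events on walking.

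**Working it through.** **Inputs from the SAP article.** 12-month recurrence 30% (control) and 22.5% (intervention); 349 planned per group, 80% power, two-sided 0.05, 24-month accrual, 12-month follow-up, 1% loss per month (Sample size and randomisation); 701 randomised, so about 350 per arm (Background).

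**Assumptions.** The article gives no rate for events other than back pain and no rate at which recurrences are reported again as adverse events. Both are varied below. Recurrence and other events are taken as independent.

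**Step 1. The plan's own figure.** It gives none for adverse events, so the check is on the sample size that supplies the recurrence rates.
- Exponential hazards give HR = ln(0.775)/ln(0.70) = 0.715.
- Events (Schoenfeld) = 4 × (1.960 + 0.842)² / (ln 0.715)² = 278.1, rounded up to 279.
- Uniform accrual with the stated loss gives a mean event probability of 0.400, so 279 / 0.400 / 2 ≈ 349 per group.

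The stated figure is reproduced, and the 30% and 22.5% rates are a fair basis.

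**Step 2. Effect of counting recurrences.** Let s be the share of recurrences re-reported as adverse events, and c and t the other-event rates in control and intervention.
- Control total = 1 − (1 − c)(1 − 0.30s)
- Intervention total = 1 − (1 − t)(1 − 0.225s)
- Intervention minus control = (t − c) − s × [0.30(1 − c) − 0.225(1 − t)]

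For c = 3% and t = 6% this is 0.03 − 0.0795s, which is zero at s = 0.03/0.0795 = 0.377.

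| Share re-reported (s) | Control | Intervention | Difference (points) |
|---|---|---|---|
| 0 | 3.0% | 6.0% | +3.0 |
| 10% | 5.9% | 8.1% | +2.2 |
| 25% | 10.3% | 11.3% | +1.0 |
| 50% | 17.6% | 16.6% | −1.0 |
| 100% | 32.1% | 27.2% | −5.0 |

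The threshold depends on the assumed rates. For 10% v 5% it is 0.05/0.0825 = 61%; for 12% v 5% it is 0.07/0.087 = 80%.

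**Step 3. Fisher's test at 350 per arm (exact enumeration).** For other events at 10% v 5%, power to show an excess on walking is 67% with recurrences left out and 0.2% with all of them counted (totals 30.3% v 33.5%). The second figure is the worst case, s = 100%.

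**Step 4. What a p-value alone leaves out.** With recurrences left out, power for a doubling from 1% to 2% is 11%, from 2% to 4% is 27%, and from 3% to 6% is 42%. The 95% CI half-width at 6% v 3% is 1.96 × √[(0.06 × 0.94 + 0.03 × 0.97)/350] = 0.031, or 3.1 points. As an example, 28 v 18 participants with an event out of 350 each gives Fisher p = 0.17. The risk difference is 10/350 = +2.9 points, 95% CI −0.8 to +6.5. The p-value alone reads as no difference; the interval shows that an excess of six points is not excluded.

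**The case against.** The strongest reply is that the article nowhere says recurrences are counted. Recurrence has its own monthly questionnaire, adverse events a separate quarterly report, and the low expected incidence suggests that recurrences were not meant to count. A recording rule of this kind may also stand in the protocol, which is not shown. This stands in part: a reader might infer that the adverse-event total includes recurrences, and the text does not support that. But the article sets out its own definition and its own test, and on that definition the content of the tested total is not settled.

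A reader might also infer that only p-values are reported, or that the analysis cannot show whether walking adds risk. Neither is supported. Table 3 gives events, participants and percentages per arm by coded type. Back pain could therefore be separated descriptively, and a risk difference can be derived from the participant counts. The general rule on confidence intervals could be read as covering Table 3. What remains is that the by-type rows carry no comparison or interval, their categories are settled from the final free text, and the planned test is on the total.

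The sign reversal is not established either: it needs a re-reporting share that the article does not give, and at a low share the harm stays visible. The serious adverse-event total is little exposed, because a recurrence enters it only if it meets a seriousness criterion such as hospitalisation.

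Finally, low power for rare harms follows from a sample sized on the primary outcome, and Fisher's test is a conventional choice for sparse counts. Neither is a fault of the plan. An interval would not reduce the imprecision, but it would show it.

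**Conclusion.** The point holds in a limited form. The adverse-event definition does not exclude recurrences, and counting them would conflict with the low incidence given as the reason for Fisher's test. The tested total can then mix benefit with harm. The size depends on two unknowns. At assumed other-event rates of 6% v 3%, the 3-point excess falls to 1 point if a quarter of recurrences are re-reported, is lost at about 38%, and becomes a 5-point deficit if all are. At higher assumed rates of other events the reversal needs 61% to 80%. All of this assumes independence of recurrence and other events.

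Separately, and whatever the counting rule, Table 3 does not carry through the article's own rule on confidence intervals, although the objective concerns added risk. At 6% v 3% the unreported uncertainty is about 3.1 points either side.

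The matter bears on the safety conclusion only. It is an inexpensive improvement to make before the data are unmasked.

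**What to change.** 1. State that low back pain recurrences, already captured as trial outcomes, are tabulated on a separate row, and that the adverse-event and serious adverse-event totals are reported without them. Totals with them may be added as a second line. Fix the rule before the masked review.
2. Add a column to Table 3 with the risk difference and 95% CI for participants with at least one adverse event and for participants with at least one serious adverse event, in line with Analysis principles and the layout of Table 2.
3. State that the safety conclusion rests on the interval, with Fisher's p-value kept alongside, and that a non-significant result will not be read as absence of added risk.

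The cost is one coding rule, one extra column and a sentence on interpretation. The data are already being collected, and the primary analysis does not change.
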